## Abstract

**Introduction:**

Atrial fibrillation (AF) is the most common sustained cardiac arrhythmia, with catheter ablation increasingly recommended as first-line therapy. Despite its effectiveness, 15% to 20% of patients require reassessment within the first month post-procedure. Standard follow-up relies on scheduled consultations and intermittent monitoring, which may delay recognition of recurrence or complications. Remote patient monitoring through conversational agents may address these gaps, yet evidence on feasibility and implementation in post-ablation care remains limited. This study aims primarily to evaluate the feasibility, usability, and acceptability of PROMBot-HSM-AF (Chatbot Platform to Collect Patient-reported Outcomes After AF Ablation, Santa Marta Hospital) during the first 3 months following AF catheter ablation.

**Methods and analysis:**

PROMBot-HSM-AF is a single-center, open-label, randomized controlled pilot (feasibility) trial with two parallel groups, conducted at Santa Marta Hospital, Lisbon, Portugal. Seventy-six patients undergoing AF ablation will be randomized in a 1:1 ratio to either chatbot-supported follow-up or standard care. The primary feasibility parameters are: recruitment rate (proportion of eligible patients consenting), retention rate at 3 months, and chatbot engagement rate (proportion of chatbot prompts answered). Acceptability and usability will be assessed using behavioral indicators (engagement and retention), the System Usability Scale (SUS), the Post-Study System Usability Questionnaire (PSSUQ), and semi-structured interviews with patients and healthcare professionals. Quantitative data will be analyzed descriptively with exploratory between-group comparisons. Semi-structured interviews with patients and healthcare professionals will be analyzed using thematic content analysis.

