In the first month, chatbot interactions will occur daily, focusing on post-ablation symptom surveillance and medication adherence. After that, the cadence will taper to reduce burden in later weeks while maintaining essential monitoring. Chatbot prompts will remain open for 24 h, after which nonresponses will be recorded as missing data. A study nurse or physician will review patient entries weekly and may proactively contact participants reporting concerning symptoms or lapses in engagement. PROMBot-HSM-AF will not replace routine follow-up; all patients will continue standard clinical care, with chatbot data available to the study clinical team to complement or inform consultations at the treating cardiologist’s discretion.

At the end of the 3-month follow-up period, all participants will undergo post-intervention assessments during a routine hospital visit. If necessary, these assessments will be conducted via secure videoconference. The PROMs will focus on the effect of AF on health-related quality of life. Participants in the intervention group will also complete validated measures of usability and perceived usefulness. They will also take part in a brief semi-structured interview to share their experience of using the chatbot. Semi-structured interviews will also be conducted with healthcare professionals directly involved in patient care (e.g., cardiologists, nurses, and technicians). These interviews are intended to elicit qualitative insights regarding their experience with the chatbot-based intervention, as well as their perceptions of its usability, clinical relevance, and impact on workflow integration.

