#### Control group

2.7.2

Participants allocated to the control group receive standard post-ablation care as delivered at Santa Marta Hospital, which includes structured discharge instructions with written educational materials about post-ablation care, scheduled follow-up appointments at 1 month and 3 months post-discharge, open access to the cardiology clinic telephone line during working hours for clinical concerns, and a 24-h hospital telephone service for urgent medical issues. Control group participants do not receive remote monitoring between scheduled appointments.

Both intervention and control groups complete identical standardized assessments at baseline (pre-discharge) and 3 months post-ablation. The timing of data collection activities is outlined in Table 1.

**Table 1 T1:** Schedule of enrollment, interventions, and assessments for the PROMBot-HSM-AF trial.

TRIAL PERIOD		Enrollment	Post-randomization				
Timepoint	Arm	⩽ day 0	Day 0	M1	M2	M3	M12
Target window		up to day 0	day 0	30±3 d	60±5 d	90±5 d	365±14 d
ENROLLMENT							
Eligibility screen	I+C	X					
Informed consent	I+C	X					
Randomization/allocation	I+C		X				
INTERVENTIONS							
PROMBot-HSM-AF	I			X	X	X	
Standard care	C		X	X	X	X	
PRIMARY OUTCOMES (FEASIBILITY)							
Recruitment rate	I+C	X	X				
Retention rate	I+C					X	
Engagement rate	I			X	X	X	
BASELINE CHARACTERISTICS							
Demographics	I+C		X				
AF history & comorbidities	I+C		X				
Procedure-related characteristics	I+C		X				
CLINICAL OUTCOMES (HOSPITAL-REPORTED)							
AF recurrence (AAD/cardioversion/repeat ablation)	I+C			X	X	X	X
Complications (readmission, ED visit, thromboembolism, major bleeding, tamponade)	I+C			X	X	X	X
All-cause mortality	I+C						X
Cardiology/internal-medicine consultations	I+C					X	X
Diagnostic tests (ECG, Holter)	I+C			X	X	X	X
PROMs							
AFEQT	I+C		X			X	
ESC quality-indicator items (weekly, rotating)	I			X	X	X	
Symptom checklist	I			X	X	X	
Medication adherence	I			X	X	X	
BIOSIGNALS							
Body mass	I			X	X	X	
Blood pressure	I			X	X	X	
Heart rate	I			X	X	X	
Step count	I			X	X	X	
ACCEPTABILITY & USABILITY							
Patient experience (SUS, PSSUQ, interview)	I					X	
Healthcare-professional experience (SUS, PSSUQ, interview)	HCP					X	

The schedule follows the SPIRIT figure convention (34).

M, month; d, days. Arm: I = intervention; C = control; HCP = healthcare professionals.

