#### Primary outcomes (feasibility)

2.9.1

The primary outcomes of this trial are feasibility parameters, including recruitment rate (eligible patients providing consent), retention rate (participants completing the 3-month follow-up), and engagement rate (proportion of chatbot prompts answered within 24 h) (36, 37).

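### Retention is listed as a behavioural indicator of chatbot acceptability, but it does not register patients who abandon the chatbot and stay in the study, and engagement can miss abandonment after week 4

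*Protocol article*

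**What the plan says.** The abstract (Methods and analysis) states: "Acceptability and usability will be assessed using behavioral indicators (engagement and retention"), followed by SUS, PSSUQ and interviews. Section 2.9.1 gives the two definitions: "retention rate (participants completing the 3-month follow-up") and "engagement rate (proportion of chatbot prompts answered within 24 h").

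On the 3-month assessment, section 2.7.1 says "all participants will undergo post-intervention assessments during a routine hospital visit", and adds: "If necessary, these assessments will be conducted via secure videoconference". The same section states that "PROMBot-HSM-AF will not replace routine follow-up; all patients will continue standard clinical care". Section 2.7.2 lists "scheduled follow-up appointments at 1 month and 3 months post-discharge" as part of standard care, and says: "Both intervention and control groups complete identical standardized assessments at baseline (pre-discharge) and 3 months post-ablation". Table 1 records retention in both arms at month 3 and engagement in the intervention arm only.

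The Introduction sets progression thresholds of 80% for retention and 70% for engagement. Section 2.9.4 and the Discussion describe daily collection for about the first four weeks and weekly collection after that. Section 2.7.1 sets the chatbot period at 12 weeks.

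**The concern.** A behavioural indicator of acceptability should change when patients stop using the thing being judged. Retention as defined changes when patients leave the study or miss the month-3 assessment. Attendance at a visit that belongs to usual care need not depend on whether the chatbot is still in use, and half of the patients counted never receive it.

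The natural reply is that engagement, the paired indicator, fills the gap. It does so for early abandonment. But it is a proportion of prompts and the prompt schedule is front-loaded, so a patient who answers throughout month 1 and then stops may already have answered most of the prompts. Both behavioural indicators could then look favourable although much of the arm had given up the platform for two of the three months. The pilot's results are meant to inform refinement of the chatbot and a definitive trial, so that pattern should be visible in the results.

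**Working it through.** **Definitions side by side.** Take a chatbot-arm patient who stops answering and attends at month 3.

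- Retention (2.9.1): follow-up completed, so retained. No other section changes this. Section 2.7.1 records unanswered prompts as missing data, and section 2.7.4 makes three consecutive missed responses an alert; neither makes the patient a dropout.
- Engagement (2.9.1): falls by the share of prompts that come after the stopping point.

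**Inputs.** The chatbot arm has 38 patients and the trial 76 (section 2.4). Daily contact for 28 days plus weekly contact for 8 weeks gives 28 + 8 = 36 prompt-days per patient. The article does not state a prompt count, so 36 is an assumption. I also assume full response until stopping and that all 76 patients complete month 3.

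**Formula.** If *a* of 38 patients stop after *d* prompt-days, engagement = [(38 − *a*) × 36 + *a* × *d*] / (38 × 36), with 38 × 36 = 1,368.

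| Stopping | Calculation | Engagement | Retention |
|---|---|---|---|
| 19 after day 7 | (684 + 133)/1,368 | 59.7% | 100% |
| 38 after day 7 | 266/1,368 | 19.4% | 100% |
| 19 after day 28 | (684 + 532)/1,368 | 88.9% | 100% |
| 38 after day 28 | 1,064/1,368 | 77.8% | 100% |

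Retention is the same in every row. Engagement falls below 70% in both early cases and stays above it in both late cases.

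**Sensitivity to the prompt count.** Let *w* be the share of prompts falling in weeks 1–4. If everyone stops after day 28, engagement is *w*, which passes when *w* ≥ 70%. If half stop, it is (1 + *w*)/2, which passes when *w* ≥ 40%. Three ways of counting:

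- 36 prompt-days: *w* = 28/36 = 77.8%. Half stopping gives 88.9% and all stopping gives 77.8%; both pass.
- One prompt per measure for body mass, blood pressure, heart rate and symptoms (daily, then weekly), plus a daily step-count prompt to the end, since section 2.9.4 states no taper for steps. Weeks 1–4: 5 × 28 = 140. Weeks 5–12: 4 × 8 + 56 = 88. *w* = 140/228 = 61.4%. Half stopping gives 80.7%, which passes; all stopping gives 61.4%, which fails.
- One prompt-day on each of 84 days: *w* = 28/84 = 33.3%. Half stopping gives 66.7% and all stopping gives 33.3%; both fail.

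**Why retention should be shown by arm.** If it were pooled, 61/76 = 80.3% would meet the threshold. With all 38 controls retained, that needs only 61 − 38 = 23 chatbot patients, and 23/38 = 60.5%.

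**The case against.** Several counter-arguments have weight.

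*Retention is not blind to rejection.* A reader might infer that retention cannot detect rejection of the chatbot at all. The article does not support that. Patients may withdraw at any time, and one who rejects the chatbot by withdrawing or by missing month 3 lowers retention. Since retention is recorded in both arms, excess loss in the chatbot arm could be seen. The gap is limited to abandonment without leaving the study.

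*Retention does not stand alone.* Engagement, SUS, PSSUQ and interviews all bear on acceptability, and staff review lapses in engagement weekly. This stands, and early abandonment would show. Late abandonment is not reliably captured by the two behavioural measures. The interviews may explain it, but section 2.10.2 plans only 10 to 15 of them.

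*The link rests on the abstract.* The Introduction refers to behavioural indicators without naming retention, section 2.9.5 assesses usability and acceptability without it, and nowhere does the article say that reaching 80% will be read as acceptability. This is fair and limits the weight of the point. The abstract nonetheless names retention explicitly.

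*Follow-up without the AFEQT.* A reader might also infer that follow-up could be counted as complete from hospital records with no month-3 AFEQT. That is speculative: sections 2.7.1 and 2.7.2 and Table 1 place the AFEQT within the 3-month assessment, and aim 3 covers PROM completeness separately.

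*PROMs by chatbot.* Section 2.9.4 says that all PROMs are collected through the chatbot. If that covers the intervention arm's month-3 AFEQT, completion could depend partly on chatbot use. The statement does not fit the AFEQT being scheduled in controls, who have no chatbot, so it does not settle the matter.

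**Conclusion.** The point holds in a limited form. As defined, retention measures completion of the trial in both arms. It does not register patients who abandon the chatbot but complete month 3, so it is a weak and non-specific indicator of chatbot acceptability. Engagement compensates for early abandonment but may not for abandonment after week 4. With 36 prompt-days, half the arm stopping after day 28 leaves engagement at 88.9%, and the whole arm stopping leaves it at 77.8%, with retention at 100% in both cases. These figures rest on an assumed prompt count, full response before stopping and complete attendance. The half-stop case passes 70% if at least 40% of prompts fall in weeks 1–4, and the all-stop case only if at least 70% do. The acceptability assessment as a whole is not blind to rejection, and retention remains sound as a trial-feasibility outcome.

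**What to change.** 1. In the abstract, remove retention from the behavioural indicators of acceptability. Keep it in section 2.9.1 as a trial-feasibility outcome and report it by arm.
2. Base behavioural acceptability on engagement, reported overall and separately for weeks 1–4 and weeks 5–12.
3. Add a persistence measure in the chatbot arm from the time-stamped data already collected (section 2.8): for example, the proportion of the 38 who answer at least one prompt during weeks 9–12, with time to last answered prompt. Requiring an answer in every one of those weeks would be too strict. With weekly prompts open for 24 hours, one missed prompt would class an active user as non-persistent.

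The cost is a wording change and one or two log-derived variables, with no new data collection. The acceptability figure may turn out less favourable.

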**Conclusions:**

This pilot trial will provide preliminary evidence on the feasibility and acceptability of integrating a chatbot-based platform into routine post-ablation care. Findings will inform refinement of the intervention and future effectiveness research in this population. The study addresses a critical gap in remote patient monitoring for post-procedural care.

**Clinical Trial Registration:**

https://clinicaltrials.gov/study/NCT07237178, identifier NCT07237178.

## Introduction

1

Atrial fibrillation (AF) is the most prevalent sustained cardiac arrhythmia, affecting 2% to 4% of the global population (1, 2). Prevalence increases with age, and projections estimate that up to 17.9 million individuals in Europe will be affected by 2060 (3, 4). AF is strongly associated with cardiovascular comorbidities including hypertension, diabetes mellitus, and heart failure, and increases the risk of stroke fivefold and all-cause mortality twofold (3, 5). These epidemiological trends underscore the need for scalable and sustainable strategies to optimize AF management.

Catheter ablation is increasingly utilized as first-line therapy in selected patients, as recommended by the European Society of Cardiology and the American College of Cardiology/American Heart Association guidelines (6). While ablation effectively improves symptoms and quality of life, a substantial proportion of patients experience recurrence or complications requiring reassessment. Studies indicate that 15% to 20% of patients require evaluation within the first month post-ablation, and up to 45% within the first year (7, 8). Current follow-up strategies predominantly rely on scheduled in-person consultations and intermittent monitoring, approaches that may delay recognition of recurrence or complications (9–11).

Remote patient monitoring (RPM) has emerged as a promising strategy to enhance continuity of care and enable early detection of clinical deterioration (12, 13). RPM encompasses telemonitoring, telemedical interventions, and structured patient education delivered through digital platforms (14). Systematic reviews support the effectiveness of RPM in improving cardiovascular outcomes, though effect sizes vary across populations and intervention designs (15). Conversational agents, commonly referred to as chatbots, represent a specific modality of RPM that may facilitate behavior change and increase patient engagement across diverse populations and age groups (16). In cardiovascular care, recent studies have demonstrated promising results, for instance, Fukuoka et al. (17) reported increased awareness of myocardial infarction symptoms among women using a chatbot intervention, and Trivedi et al. (18) documented high engagement rates with artificial intelligence-driven follow-up telephone calls after AF hospitalization.

Despite these advances, several critical knowledge gaps persist. First, evidence regarding the implementation of RPM specifically in post-procedural contexts, including after AF catheter ablation, remains limited (19). Second, although RPM has been associated with improvements in functional status and reduced acute care utilization, its effects on broader clinical outcomes and health-related quality of life remain inconclusive (20). Third, current European guidelines highlight gaps in patient-centered management, particularly regarding the role of RPM and telemedicine in AF care (21). Successful adoption of RPM requires not only appropriate technology but also coordinated multidisciplinary healthcare teams, robust patient engagement strategies, and integration into existing clinical workflows (22, 23).

These gaps underscore the need for studies evaluating co-created, patient-centered digital interventions that systematically integrate patient-reported outcome measures (PROMs) into AF follow-up care. The PROMBot-HSM-AF (Chatbot Platform to Collect Patient-reported Outcomes After AF Ablation, Santa Marta Hospital) was developed through a participatory co-creation process involving cardiologists, nurses, patients, engineers, and health scientists to address these needs and optimize the feasibility of real-world implementation. The platform is delivered through WhatsApp, leveraging a widely adopted messaging service with 73% penetration in Portugal overall and 62% among adults aged 55 to 64 years (24). Unlike standard follow-up, which offers limited early post-ablation contact and no routine PROM capture, structured digital PROM collection has been associated with earlier detection of arrhythmia recurrence in comparable post-ablation populations (13), suggesting potential to complement existing care through more timely clinical response.

The primary objective of this pilot study is to evaluate the feasibility and acceptability of integrating PROMBot-HSM-AF, a chatbot-based platform for collecting PROMs and clinical parameters, into routine post-ablation follow-up care at a tertiary hospital. The specific aims, framed for the feasibility and pilot phase, are to: (1) quantify recruitment, retention, and engagement rates over the 3-month follow-up and compare each against pre-specified progression thresholds (retention ⩾80%, engagement ⩾70%), constituting the primary outcomes; and, as secondary, exploratory outcomes, (2) assess the usability and acceptability of the chatbot (patients) and of the clinical monitoring interface (healthcare professionals) at 3 months, using validated usability measures (System Usability Scale [SUS], Post-Study System Usability Questionnaire [PSSUQ]), behavioral indicators, and semi-structured interviews; and (3) evaluate the preliminary integration and data completeness of PROMs (e.g., Atrial Fibrillation Effect on Quality-of-Life [AFEQT]) collected via the platform over the 3-month follow-up, and explore between-group differences as hypothesis-generating estimates to inform a definitive trial.

## Methods and analysis

2

### Study hypotheses

2.1

We hypothesize that integrating PROMBot-HSM-AF into routine post-ablation follow-up care will be feasible and acceptable, and that structured, high-frequency remote data collection will be associated with improved patient engagement in follow-up care and more favorable trends in health-related quality of life (AFEQT) relative to standard care.

### Study design

2.2

This study is a single-center, open-label, randomized controlled pilot (feasibility) trial with two parallel groups. Patients undergoing catheter ablation for AF will be randomly assigned 1:1 to chatbot-supported follow-up via the PROMBot-HSM-AF platform (intervention) or standard care (control). The control arm comprises structured discharge education and scheduled 1- and 3-month appointments without remote monitoring between visits (detailed under Procedures). The study flow diagram (Figure 1) represents the feasibility pathway.

**Figure 1 F1:**
[figure not shown]
Flowchart diagram for the study PROMBot-HSM-AF.

### Study setting

2.3

The feasibility study is conducted at the Department of Cardiology, Santa Marta Hospital, Lisbon, Portugal. This tertiary referral center specializes in cardiothoracic care and performs a high volume of cardiac ablation procedures annually. Since 2011, the hospital has implemented a structured 1-year follow-up program involving periodic telephone consultations, creating a strong organizational foundation for digital health integration (25, 26).

Participant recruitment, informed consent procedures, and clinical assessments occur at the hospital. The intervention is delivered remotely, with patient-chatbot interactions occurring in participants’ home environments. Clinical coordination and data monitoring are centralized at the hospital to ensure integration with standard care pathways.

#### Inclusion criteria

2.3.1

Patients are eligible for enrollment if they meet all of the following criteria:
Age 18 years or older;Documented diagnosis of paroxysmal or persistent AF based on clinical assessment and coded according to the International Classification of Diseases, 11th Revision;Undergone catheter ablation for AF at Santa Marta Hospital during the study recruitment period;Able to use the PROMBot-HSM-AF chatbot independently or with caregiver assistance (Portuguese literacy sufficient to follow instructions and ability to operate a smartphone); digital literacy is assessed individually, with caregiver-assisted enrollment available for older adults willing to learn;Clinically stable at discharge, defined as absence of any complication requiring continued inpatient care or urgent reintervention (e.g., cardiac tamponade, major access-site bleeding, high-grade atrioventricular block); minor, self-limiting findings (e.g., uncomplicated groin haematoma) do not preclude participation;Provision of written informed consent.

#### Exclusion criteria

2.3.2

Patients are excluded if they meet any of the following criteria:
Severe cognitive impairment preventing comprehension of study procedures, such as moderate-to-severe dementia or other neurological conditions limiting capacity to consent;Severe uncorrected visual impairment or motor disability preventing smartphone operation even with caregiver support;Explicit refusal to use digital technology or unwillingness to share health data required for the study;Clinical or contextual conditions rendering 3-month follow-up unfeasible, including anticipated relocation outside the hospital catchment area or concurrent participation in another interventional study with overlapping endpoints;Life expectancy less than 6 months.

